## Abstract

**Background:**

Cricopharyngeal dysfunction (CPD) occurs in various neurological disorders, especially stroke. The treatment approaches of CPD include swallowing training, cricopharyngeal dilation, botulinum toxin (BTX) injection, and cricopharyngeal myotomy. BTX injection into the cricopharyngeal muscle is effective and safe for some patients with dysphagia, with a success rate between 43 and 100% (mean = 76%). However, well-designed randomized controlled clinical trials are needed to verify its efficacy and safety for the treatment of CPD. The objective of this study is to explore the efficacy and safety of BTX for neurogenic cricopharyngeal achalasia, when administering an injection into the cricopharyngeal muscle guided by a novel precise positioning method, that combines ultrasound, catheter balloon, and electromyography (BECURE).

**Methods:**

BECURE is a single-center randomized, placebo controlled, double-blinded, superiority clinical trial. To detect a significant difference between the 2 groups, a sample size of 44 patients is estimated. The intervention is BTX versus placebo, with 1:1 randomization. The randomization sequence from 1 to 44 was generated using the Statistical Package for Social Sciences. The study is divided into two phases. In the first phase, patients will be injected with BTX or the placebo. In the second phase, patients who received a placebo injection and those who did not respond to the first BTX injection will receive an injection of BTX. The primary outcome is the score of the Functional Oral Intake Scale (FOIS). The secondary outcomes are as follows: upper esophageal sphincter (UES) residual pressure, UES resting pressure, duration of UES relaxation, velopharyngeal and laryngopharyngeal peak pressure, UES opening, pharyngeal construction ratio, residue of bolus in the epiglottis valley or piriform sinus, and penetration and aspiration.

**Discussion:**

Dysphagia is a common complication of stroke. There is lack of high-quality evidence for the efficacy of BTX in treating neurogenic CPD. This study will clarify whether BTX injection into the cricopharyngeal muscle can be effective and safe for patients with stroke and CPD.

**Trial registration:**

Chinese Clinical Trial Register (ChiCTR1900025562). Registered on September 1, 2019.

## Background

Functional swallowing occurs due to a series of well-coordinated movements that allow transport of food bolus from the oral cavity into the stomach while avoiding passage of food bolus into the airway [1]. Dysphagia occurs due to neurological disorders that impair the transport of food from the oral cavity to the stomach efficiently and/or safely [2] and is associated with an increased risk of pulmonary complications, dehydration, malnutrition, and mortality [1, 3]. Dysphagia is a common complication in stroke patients with a morbidity rate between 20 and 90%, depending on the assessment methods [4].

The upper esophageal sphincter (UES) is the high-pressure physical barrier to the transport of a food bolus or liquids between the pharynx and esophagus. The cricopharyngeal muscle is main muscle responsible for UES function [5]. This muscle remains in a contracted position during respiration, preventing air from entering into the esophagus and relaxes and opens during swallowing or vomiting [2]. Cricopharyngeal dysfunction (CPD), characterized by difficulty of food bolus entering the esophagus, occurs often due to 3 main factors: cricopharyngeal muscle spasm, incomplete laryngeal movement, and insufficient descending pressure of the bolus [2].

Cricopharyngeal achalasia is one of the main manifestations of CPD characterized by an uncoordinated state of relaxation or spasm of the cricopharyngeal muscle. Primary cricopharyngeal achalasia is a rare, idiopathic disorder [6]. Secondary cricopharyngeal achalasia occurs in various disorders, including stroke, Parkinson’s disease, and head and neck cancers [7]. Cricopharyngeal achalasia is one of the main causes of dysphagia after stroke [8]. Many swallowing problems recover spontaneously within 7 days after stroke, but approximately 8 to 50% of patients experience persistent difficulties in swallowing 6 months after stroke [9, 10]. The prevalence rates of dysphagia vary due to differences in the definition of dysphagia, method of assessing swallowing function, timing of swallowing assessment after stroke, and number and type of patients with stroke studied [11]. Early therapy for dysphagia is effective and can reduce serious complications [12]. For patients with persistent dysphagia, more effective treatments are needed to reduce morbidity and mortality.

Several approaches exist for treating CPD, including swallowing rehabilitation, cricopharyngeal balloon dilation, botulinum toxin (BTX) injection, and cricopharyngeal myotomy [13]. Cricopharyngeal myotomy, a traditional surgical method, is the optimal choice for primary cricopharyngeal achalasia. However, its effectiveness for cricopharyngeal achalasia is considered unsatisfactory [14]. Furthermore, cricopharyngeal myotomy is unsuitable for patients in poor medical condition. Balloon dilation for neurogenic dysphagia has been widely used in clinical practice, and its usefulness has been supported [15]. However, we found that the swallowing function of some patients failed to improve even after prolonged balloon dilation. In one systematic review, the success rate of dilation was between 58 and 100% (mean = 81%) [13]. For patients with cricopharyngeal achalasia, BTX injection is useful [7, 16–18]. The success rates of BTX injection vary between 43 and 100% (mean = 76%) [13]. The effective duration varies depending on the injection site, dosage, and etiology of disease [19]. Currently, there is no high-quality evidence for the efficacy of BTX on neurogenic dysphagia [7, 8]. Thus, well-designed, randomized controlled clinical studies are needed to verify the efficacy and safety of BTX and to provide evidence for clinical applications.

The precise localization of the cricopharyngeal muscle during BTX injection is difficult to obtain and has been the focus of several studies. Since 1994, when Schneider [20] first described BTX injection into the cricopharyngeal muscle as an alternative to surgery, many researchers have tried different localization methods to ensure the efficacy of this treatment. Initially, BTX was injected under direct visualization during transcervical surgery and general anesthesia. Later, investigators attempted injecting BTX percutaneously, under the guidance of electromyography (EMG) or endoscope [16, 18, 21, 22]. Some researchers have injected BTX with the guidance of computed tomography (CT), which was shown to be effective and safe [23]. However, each guiding techniques has disadvantages if used alone. A new localization method will be used in this study, which is guided using ultrasound, catheter balloon, and EMG.

Here, we present a study protocol designed to explore the efficacy and safety of BTX injection guided by ultrasound, catheter balloon, and EMG for treatment of neurogenic cricopharyngeal achalasia.

## Methods and design

### Objective

To explore the efficacy and safety of BTX for treatment of neurogenic cricopharyngeal achalasia, with BTX injection guided by ultrasound, catheter balloon, and electromyography, a novel precise positioning method.

### Design

The administration of BTX (BOTOX, Allergan, Inc., Irvine, CA, USA) for cricopharyngeal dysfunction guided by a combination of catheter balloon, ultrasound, and electromyography in patients with stroke (BECURE) is a prospective, randomized controlled, double-blinded, superiority, single-center clinical trial. This study was approved by the Ethics Committee of the Third Affiliated Hospital of Sun Yat-sen University ([2019]02-419-01).

### Patient population

Patients with stroke and dysphagia who failed to improve after at least 1 week of conventional dysphagia rehabilitation treatment, including balloon dilation.

### Study setting

This study will be conducted in an academic hospital, the Third Affiliated Hospital, Sun Yat-sen University in Guangdong Province, China.

### Inclusion criteria

Patients are eligible for study participation if they fulfill all of the following criteria:
Meet the diagnostic criteria for stroke, listed in the *Diagnostic criteria of cerebrovascular disease in China (version 2019)* [24].Stable vital signs without severe cardiopulmonary diseaseAged 18–90 yearsFailed in swallowing function improvement after 1 week of balloon dilationFunctional Oral Intake Scale (FOIS) Score ≤ 2Cricopharyngeal muscle cannot completely open, verified by video fluoroscopic swallowing study (VFSS); moderate-severe residue in epiglottic valley or piriform sinus, evaluated by flexible endoscopic evaluation of swallowing (FEES).UES residual pressure > 20 mmHg by high-resolution manometry (HRM).Cooperation with treatment without dysfunction of hearing and comprehension.Provide informed consent on their own behalf (or by legally appointed representatives/authorities).

### Exclusion criteria

Patients will be excluded from study participation if any of the following apply:
Suffer from other neurogenic dysphagia or a condition that can cause dysphagia (for example, Parkinson’s disease).Have a non-neurogenic disease (e.g., cancer).Have a neuromuscular disorder (e.g., myasthenia gravis or motor neuron disease).Have psychopathy.Unable to cooperate with examination and treatment.Have infections or cuts at injection site.Allergic to botulinum toxin.Have coagulation dysfunction.Receive or have received anesthetics or any medicine that affects neuromuscular junctions within 1 month prior to participation.Participating in another study that could influence the results of BTX injection on the cricopharyngeal muscle.

### Drop out criteria

Participants are found to be unable to complete the follow-up on time, or there is an unpredictable condition such as severe adverse event.Participants require not to participate in this research.

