### Treatment or intervention

The treatment will comprise of administering a BOTOX injection into the cricopharyngeal muscle guided by a combination of catheter balloon, ultrasound, and EMG. The BOTOX will be diluted to 100 U/ml with normal saline. Patients will receive 50 U (diluted in 0.5 ml normal saline) of BOTOX or a placebo (0.5 ml normal saline) in the cricopharyngeal muscle. First, the catheter balloon will be inserted into the esophagus through the nasal cavity, and 4 to 6 ml of water will be injected into the balloon. The balloon will be fixed at the cricopharyngeal muscle when pulled up softly and cannot be pulled up more. One person (speech language pathologist) will hold the catheter and maintain the balloon at this position. Second, ultrasound probe will be placed on the left or right side of the anterior cervical region. Under the guidance of ultrasound, the sternocleidomastoid muscle, thyroid gland, cricopharyngeal muscle, and balloon will be visible. The balloon, as a reference, will be fixed at the distal part of the cricopharyngeal muscle. The concentric EMG needle will be inserted in the marked side under the guidance of ultrasound. When the needle passes through the tissue and reaches the cricopharyngeal muscle, the EMG signal of this muscle can be heard, and then the patient will be instructed to swallow, allowing changes in the EMG signal to be observed and heard. After confirming the position, BOTOX will be injected into the target muscle. Generally, a single injection of botulinum toxin is 50 U. The BTX intervention will be applied by the PI ([name]) assisted by other investigators. Participants will remain hospitalized for the duration of the research. Every concomitant care and conventional dysphagia rehabilitation treatment will be allowed. Novel rehabilitation treatment such as repetitive transcranial magnetic stimulation is prohibited during the trail.

Every effort will be made to improve patient adherence to protocols. In the case of an adverse event following treatment administration (hoarseness, gastroesophageal reflux, local bleeding, aspiration pneumonia), treatment will be immediately discontinued.

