### Data collection and management

A clinical research associate will ensure that patient inclusion and data collection are in line with the protocol and will check the following variables: patient initials, date of birth, sex, signed consent form, eligibility criteria, date of randomization, treatment assignment, adverse events, and study endpoints. The data will be collected by the clinical research associate on case report forms. The study documents will be stored and kept in a locked and secure office. All personnel involved in data analysis will be masked. Only the PI and the statisticians will have access to the final data set. If the patient drops out, all data before he/she drops out will be recorded, as well as the reason for the patient’s withdraw and any adverse event.

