### Statistical analyses

The statistical analysis will be performed using the Statistical Package for Social Sciences (SPSS) version 23.0 for Windows by a statistician who is not involved in the study. A chi-square test will be used to compare the expulsion rate between the early and late groups. If the expulsion rate of the two groups is not statistically significant (*p* > 0.05), compliance of the groups will be considered similar. On the contrary, it is considered that the compliance of the two groups of patients is inconsistent, and it is necessary to re-recruit research cases, which will be assessed by the Data Monitoring Committee. Normally distributed data will be presented as the mean ± standard deviation. Categorical data will be presented as the frequency and proportions. Assumptions of normality will be tested with the Kolmogorov-Smirnov test. The parametric data will be analyzed by the independent sample *t* test, while the non-parametric data will be analyzed by the rank sum test. The *p* values ≤ 0.05 will be considered statistically significant. A comparison between two groups will be used to assess whether the efficacy (represented by FOIS, UES residual pressure, UES resting pressure, duration of UES relaxation, etc.) is different. A chi-square test will be used to compare the differences in the proportion of patients with improved swallowing function (assessed by FOIS) between the groups. Improvement prior to and post treatment in both groups will be assessed. Efficacy evaluation indicators (FOIS, UES residual pressure, UES resting pressure, duration of UES relaxation, etc.) will be compared two weeks after the first and second injections to assess improvement in the groups. A logistic regression method will be used to establish a probability model of BTX efficacy and influencing factors. The effect of each influencing factor on BTX efficacy (OR and 95% confidence interval) will be quantitatively analyzed to determine the interpretable accuracy and reliability of the coefficient *R*^2^ evaluation of the established efficacy and influencing factors model, with the FOIS score of the BTX group will be defined into effective and non-effective, a two-category variable *Y* (FOIS ≥ 3, *Y* = 1; FOIS<3, *Y* = 0). Patients’ age, gender, stroke lesion location, UES residual pressure, UES resting pressure, duration of UES relaxation, velopharyngeal peak pressure and hypopharyngeal peak pressure, UES opening, pharyngeal construction ratio, residue of bolus in the epiglottis valley or piriform sinus, penetration, and aspiration will be used as influencing factors of variable Xi (*i* = 1, 2, …11). A chi-square test will be used to compare the incidence of adverse events between the groups. An interim analysis will be performed after inclusion of the first 22 patients by a statistician who is not involved in this research. The data collection of the study will be assessed and confirmed by the Data Monitoring Committee, which can make decision to stop the research when it is harmful or futile.

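### The drop-out criteria let a severe adverse event or missed follow-up time end outcome recording before the two-week FOIS, permitting outcome-related loss of the primary endpoint

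*Protocol article*

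**What the plan says.** All references are to the protocol article.

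- Drop out criteria: a participant becomes a drop-out when follow-up cannot be finished in time, or when "there is an unpredictable condition such as severe adverse event". The participant's own wish to leave is listed as a separate criterion.
- Data collection and management: "If the patient drops out, all data before he/she drops out will be recorded". The same sentence adds the reason for withdrawal and any adverse event. It mentions no outcome assessment after drop-out.
- Statistical analyses: the efficacy measures, FOIS among them, "will be compared two weeks after the first and second injections to assess improvement in the groups".
- Statistical analyses, on drop-outs: "A chi-square test will be used to compare the expulsion rate between the early and late groups". If p exceeds 0.05, compliance is taken as similar. Otherwise "it is necessary to re-recruit research cases", subject to assessment by the Data Monitoring Committee.
- Treatment or intervention: "Participants will remain hospitalized for the duration of the research".
- Sample size estimates: 44 patients, with 10% loss to follow-up allowed for.

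**The concern.** Two of the three drop-out triggers are events after randomisation that the patient does not choose. Either may be related to the treatment given and to how well the patient swallows. Aspiration pneumonia, which the article names among the possible adverse events, is the clearest example, because it bears directly on oral intake.

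If such an event occurs before the two-week assessment and outcome recording then ends, the patient has no post-treatment FOIS. An analysis plan can choose how to treat a missing value, but it cannot recover one that was never collected. The patients who remain are then selected by what happened after randomisation, and the comparison loses part of the protection that randomisation gives. In a trial of 22 per arm, a few such patients can move the primary result visibly.

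The loss looks avoidable, because the article keeps participants in hospital throughout.

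**Working it through.** **1. The plan's own figure.** Inputs from Sample size estimates: late (placebo) group 2.6 ± 1.1, early (BTX) group 4 ± 1.8, type I error 0.05, power 0.80, 10% loss. Sidedness is not stated, so two-sided is assumed.

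- Pooled SD = √((1.1² + 1.8²)/2) = 1.492; standardised difference = 1.4/1.492 = 0.939.
- The two-sample t test (noncentral t) needs 18.83, so 19 per arm. 19/0.9 = 21.1, so 22 per arm and 44 in total.

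The stated 44 is reproduced, and this point does not change it. Ten per cent of 22 is 2.2, so about two losses per arm are already expected.

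**2. From the drop-out rule to a missing FOIS.** A severe event before the two-week assessment meets the drop-out criterion. The data section provides for outcomes up to drop-out and none afterwards. The primary value for the placebo-controlled comparison is taken two weeks after the first injection, so it is missing for that patient. A patient dropped after that assessment keeps the value.

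**3. Does the expulsion test protect the comparison?** I read the expulsion rate as the drop-out rate; the article does not define it. For k expulsions in one arm and none in the other, 22 per arm, the Pearson statistic is 44 × (22k)² / (22 × 22 × k × (44 − k)) = 44k/(44 − k).

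| Expulsions | Pearson χ² | Pearson p | Continuity-corrected p | Fisher p |
|---|---|---|---|---|
| 3 v 0 | 132/41 = 3.22 | 0.073 | 0.23 | 0.23 |
| 4 v 0 | 176/40 = 4.40 | 0.036 | 0.116 | 0.108 |

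Three losses all in one arm pass as similar compliance. Four are flagged only by the uncorrected test. Equal counts would not show equal reasons or equal unseen outcomes either, and newly recruited patients do not supply the scores of those removed.

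**4. Size, as illustration only.** The article gives no adverse event rate. Assume that the planning means describe the patients who remain, and that each removed patient would have scored FOIS 1 (entry requires 2 or below). With k removed from an arm of 22 whose remaining mean is m, the all-randomised mean is ((22 − k)m + k × 1)/22. The reported difference is 4.0 − 2.6 = 1.40 in every row.

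| Removed before week 2 | BTX mean | Placebo mean | All-randomised difference |
|---|---|---|---|
| 1 BTX | 85/22 = 3.86 | 2.60 | 1.26 |
| 2 BTX | 82/22 = 3.73 | 2.60 | 1.13 |
| 3 BTX | 79/22 = 3.59 | 2.60 | 0.99 |
| 2 in each arm | 3.73 | 54/22 = 2.45 | 1.27 |
| 2 placebo only | 4.00 | 2.45 | 1.55 |

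If 2 BTX patients are removed who would have scored 2 instead of 1, the BTX mean is 84/22 = 3.82 and the difference 1.22. The sign and size of the distortion depend on which arm loses patients and what they would have scored.

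**The case against.** The strongest reply is that the article does not say what a critic may read into it. Several stronger readings are tempting, and the document does not support them.

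- A reader might infer that the worst BTX outcomes are excluded from the efficacy comparison. No section says whether drop-outs are excluded or kept, and the analysis set may be defined in an analysis plan that is not shown. This stands. What remains is that the value itself is not provided for.
- A reader might infer a bias in favour of BTX. The criteria apply to both arms under blinding, placebo patients receive a saline injection into the same muscle, and every patient enters with FOIS 2 or below and marked residue. Bleeding or aspiration pneumonia can occur in either arm. This stands: the direction is conditional.
- A reader might infer that harmed patients vanish from the safety data. They do not. Adverse events of drop-outs are recorded, each event's severity and outcome are documented, and incidence is compared between groups.
- A reader might treat all the named adverse events as drop-out triggers. For those the article says "hoarseness, gastroesophageal reflux, local bleeding, aspiration pneumonia), treatment will be immediately discontinued", which concerns treatment and not participation. Nothing there calls hoarseness, reflux or local bleeding severe.
- A reader might quote the two-BTX-patient case (0.27/1.40, about 19%) as the expected bias. It places every event in one arm at a score of 1, and other patterns give less or reverse the sign.

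It is also fair that patients who stay in hospital will seldom miss a due date, so the lateness criterion may have little reach. That same fact makes continued scoring easy.

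**Conclusion.** The point holds in limited form. The drop-out and data-recording rules together permit loss of the primary outcome for reasons that may depend on treatment and on swallowing, and the expulsion test with re-recruitment does not repair it. This is a stated rule and not a detail left to an analysis plan. It can bias the FOIS comparison, towards BTX if early severe events are more frequent or the unseen scores worse in that arm, and against BTX in the opposite case.

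The size cannot be derived from the document. Under the assumptions above, a reported 1.40 would correspond to an all-randomised difference between 0.99 and 1.55 across the patterns tabulated. That is a sensitivity range and not a forecast. The conclusion rests on reading the data section as ending outcome collection at drop-out; if the full protocol continues it, the article's wording should say so.

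**What to change.** - Reword Drop out criteria and Data collection and management so that stopping study treatment is separate from leaving the study, and only withdrawal of consent to data collection ends follow-up. This leaves the clinical rules on stopping treatment as they are.
- Collect the two-week FOIS on every randomised patient, and accept late assessments with their actual date.
- Replace the expulsion test and re-recruitment rule with an analysis of all randomised patients by assigned arm. Drop-out counts and reasons can still be reported by arm.
- Examine any FOIS that truly cannot be obtained in a pre-specified sensitivity analysis, for example with the worst score. Imputing FOIS 1 as the only rule would itself be debatable.

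The cost is protocol wording and a little more analysis work. Hospitalised patients need no extra visit. The observed effect may turn out slightly less favourable.
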